### Recruitment and randomization

Eligible persons presenting to the emergency department (ED) or referred from another hospital, with multiple, simple rib fractures will be informed about the trial at the ED or at the surgical ward after admission. After explanation of the study, eligible patients will receive written information and a consent form from the attending physician, the clinical investigator, or a research assistant. Patients meeting all eligibility criteria will be recruited within 1 day after hospital admission. As surgical rib fixation appears to be most beneficial when performed within 72 h after trauma, patients are stimulated to decide within this period. However, informed consent can be given by the patient as long as rib fixation can be carried out within 1 week after trauma. Should patients not be able to sign informed consent themselves, a legal representative will receive oral and written information about the study, in the hospital, by the attending physician, the clinical investigator, or a research assistant, and will be asked to consent with participation of the patient.

After signing informed consent by patient or proxy, participants are allocated to one of the two study arms (surgical stabilization or nonoperative treatment) using a web-based randomization program that will be available 24 h a day. Allocation will be at random and concealed, in a 1:1 ratio, and will be stratified by site. Variable block sizes will be used; in each block, both treatments will be represented equally. As the intervention cannot be blinded, it will in no case be necessary to break the randomization code.

As with many surgical trials, patients and surgeons cannot be blinded for the intervention. In order to reduce bias as much as possible, a research physician or research assistant will perform the follow-up measurements using a standardized protocol. Also, the treating surgeon or ICU doctor will identify the primary outcome (i.e., pneumonia) based on the definition as mentioned under outcome measures.

Participation is on a voluntary basis and participants are allowed to withdraw from the study at any time without specifying why. The general practitioner will be informed about the patients’ participation.

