#### Secondary outcome measures

The secondary outcome measures are:Need and duration of mechanical ventilation in days. The number of days of invasive mechanical ventilation (by endotracheal tube or tracheostomy) from intubation until successful weaning will be determined. The need for mechanical ventilation will be evaluated based on arterial blood gas analysis and clinical performance of the patient. The duration of mechanical ventilation will be calculated from the dates of intubation and extubation. Re-intubation within 30 days will be recorded as well.Level of thoracic pain (NRS) and analgesics use. Thoracic pain will be determined using an 11-point Numeric Rating Scale (NRS) in which 0 implicates no pain and 10 the worst possible pain. Five thoracic pain levels will be analyzed: pain in rest, at night, during daily activities (e.g., work or hobbies), during maximal inspiration, and during self-care. Analgesics use during admission will be extracted from the medical files. After discharge, analgesics use will be asked for during the follow-up visits. Daily narcotic requirement will be calculated using an equivalence scale for 30 mg/day oral morphine.(Recovery of) pulmonary function. The parameters tidal volume (TV), forced vital capacity (FVC), inspiratory capacity (IC_lung_), and forced expiratory volume at 1 second (FEV_1_) will be determined using spirometry. Spirometry will be done by a member of the research team. During the spirometry, the patient has to inhale actively and exhale with maximum force possible. The mean of three tests will be calculated.Hospital length of stay expressed in days. This will be calculated as the time between admission and discharge from the hospital. Re-admission within 30 days will be added. Re-admission for thoracic reasons after 30 days and up to 12 months will be counted separately.ICU length of stay expressed in days. This will be calculated similarly to the hospital length of stay.Thoracic injury-related complications and mortality. The occurrence of thoracic injury-related complications will be recorded from the medical charts during clinical admission and each follow-up visit. Complications will be categorized for level of severity and treatment necessity according to the Clavien-Dindo classification [43]. Complications will include empyema (as diagnosed on CT scan, in presence of fever or positive cultures in the drained fluid), (retained) hydrothorax (a heterogeneous fluid collection with Hounsfield unit readings of 35–70 and evidence of pleural thickening) [44], nonunion (diagnosed on CT scan or operatively, at least 6 months after trauma) [45], and other (all other complications as judged by the treating physician). If mortality is caused by the thoracic injury or complication of thoracic injury, it will be counted in rates of mortality. Death caused by other reasons will be noted but excluded in this calculation.Surgery-related complications. The ORIF group can also develop hardware-related complications or failure. Hardware-related complication is superficial and deep wound infection which is defined as redness, tenderness, and warmth surrounding and in direct contact with the postoperative wound. Superficial infection leads to oral or IV antibiotics, and deep infection leads to surgical activity such as stitch removal of exploration of the wound. Hardware failure is defined as loosening of the plate, secondary dislocation of fixation material, malposition of hardware, and broken plates or splints.Secondary interventions to resolve complications. Secondary interventions within 12 months after trauma to relieve pain, treat infection, or other rib fracture-related problems will include the following: antibiotic therapy (both oral and intravenous), additional surgical interventions (e.g., surgical stabilization of nonunion, evacuation of hematoma, evacuation of empyema, removal of failed hardware, symptomatic hardware removal, and treatment of infection), and additional percutaneous interventions (e.g., for persistent bleeding intercostal artery, intraparenchymal bleeding, drainage of infection, and drainage of pleural fluid).Health-related quality of life measured using the Short Form-12 (SF-12) and EuroQoL-5D (EQ-5D) questionnaires. The SF-12 analyzes global health status, functional scale, and symptom scale. The score will be calculated based on eight domains and summarized into a Physical Component Summary (PCS) and Mental Component Summary (MCS). Data will be reported as utility score, ranging from 0 to 1 with a higher value indicating better quality of life. As a reference, the US population of 1998 will be used [46]. The EQ-5D is the most commonly used quality of life instrument for (rib) fracture patients [47, 48]. The EQ-5D is recommended for assessment of quality of life in trauma patients, especially for economic evaluation [49, 50]. The EQ-5D-5 L descriptive system consists of five dimensions of health (mobility, self-care, usual activities, pain/discomfort, and anxiety/depression), each with five possible answers. The patients’ health states will be converted into a utility score using the Dutch tariff [51]. Utility scores range from 0 to 1 with lower scores indicating poorer quality of life.Cost-effectiveness and health care consumption. Economic evaluations will be done from a societal perspective. The validated Medical Consumption Questionnaire (iMCQ) and Production Consumption Questionnaire (iPCQ) will be used. iMCQ details medical specialist care, physical therapy, hospitalization, nursing home, home care, and other costs directly associated with diagnosis, treatment, and rehabilitation. iPCQ comprises work resumption and production losses. Health care costs and lost productivity until 1 year after trauma will be measured in accordance with economic guidelines [52].

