### Study procedures

Patients will be followed until 12 months after trauma. Clinical evaluation will occur daily during hospital admission. After discharge, outpatient clinic evaluation will occur at 2 weeks (window 7–21 days), 1 month (window 21–39 days), 3 months (window 11–15 weeks), 6 months (window 24–28 weeks), and 12 months (window 12–14 months). These visits are standard of care for the targeted patient group. A schedule of events is shown in Table 1. Baseline data and perioperative data will be collected from the patients’ medical files as soon as possible, but no later than the first outpatient department visit. At the 12-month follow-up contact, the surgeon or research assistant will document any secondary intervention that may be planned for the patient.

**Table 1 Tab1:** Schedule of events (duration after trauma)

Radiographs and event forms	Screening	Enrolment	Pre-surgery	Surgery	Post-surgery (until day 7*)	2 weeks (7–21 days)	30 days (21–39 days)	3 months (11–15 weeks)	6 months (24–28 weeks)	12 months^$^ (12–14 months)
CT-scan	X								X	
Screening	X									
Informed consent		X								
Randomization		X								
Baseline data			X	X						
Intervention/surgical report form				X	X					
Outpatient clinic FU						X	X	X	X	X
Spirometry							X	X	X	X
Analgesic use			Daily, afternoon		Daily, afternoon	X	X	X	X	X
Pain (NRS-rest and inspiration)			Daily, afternoon		Daily, afternoon	X**	X	X	X	X
Pain (NRS-night, daily, and care)						X**	X	X	X	X
QoL (EQ-5D and SF-12)						X**	X	X	X	X
Complications			X	X	X	X	X	X	X	X
(Secondary) interventions			X		X	X	X	X	X	X
iPCQ and iMCQ questionnaire						X***	X	X	X	X
Early withdrawal						****	****	****	****	****

*Post-surgery

^$^May be planned at the patients’ residency

**Asking for current and pre-trauma status

***Asking for pre-trauma situation

****Only if applicable.

After 6 months, a thoracic CT scan is repeated. Pulmonary function will be tested during the outpatient clinic visits at 1, 3, 6, and 12 months. At each follow-up visit, the coordinating researcher or research assistant will ascertain patient status (i.e., adverse events/complications or secondary interventions) and will verify information within the medical records. At each visit, patients will be asked to complete questionnaires relating to their pain (NRS), analgesics use, quality of life (QoL) (SF-12 and EQ-5D), and health care use (iPCQ and iMCQ).

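### Averaging three spirometry tests builds submaximal efforts into FVC and FEV1; the largest of the three would carry no more of that shortfall, and usually less

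*Protocol article*

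**What the plan says.** Under Secondary outcome measures, the entry on pulmonary function names four quantities to be determined by spirometry: "The parameters tidal volume (TV), forced vital capacity (FVC), inspiratory capacity" and FEV1. It then gives one instruction to the patient, "During the spirometry, the patient has to inhale actively and exhale with maximum force possible", and one rule for combining repeats, "The mean of three tests will be calculated". Neither sentence is limited to particular parameters, and no other section of the article qualifies the averaging rule.

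Three other places bear on the point.

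- Study procedures: "Pulmonary function will be tested during the outpatient clinic visits at 1, 3, 6, and 12 months".
- Secondary outcome measures, pain entry: pain is scored for "pain in rest, at night, during daily activities (e.g., work or hobbies), during maximal inspiration, and during self-care". Table 1 schedules the score on inspiration at every visit that has spirometry.
- Recruitment and randomization: "patients and surgeons cannot be blinded for the intervention", and "a research physician or research assistant will perform the follow-up measurements using a standardized protocol". That standardized protocol is not shown.

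**The concern.** FVC and FEV1 are defined by the patient's maximum effort. An incomplete attempt gives a reading below what the patient can achieve, and hardly ever one above it. The error is therefore mainly one-sided, and averaging does not cancel it as it would symmetric noise. Every weak attempt is built into the analysed value.

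This matters here because effort could differ between the arms. Patients know their allocation, and chest-wall pain can limit a forced breath. The Discussion names less pain as a hoped-for benefit of surgery. The Background reports chest-wall pain in 64% of patients with isolated multiple rib fractures at 2 years, so a first test at 1 month does not remove the issue. If weak attempts are rarer in one arm, averaged FVC and FEV1 differ between arms even with equal lung capacity. The Background presents lung function as a matter of lost lung capacity and calls the existing spirometry comparisons contradictory. A summary that is more sensitive to effort than it needs to be makes this trial's result harder to read.

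**Working it through.** The article states no figure for spirometry, so there is nothing to reproduce. The check is a short argument about the two summaries, followed by illustrations whose inputs are assumptions.

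**Step 1, one session.** Let M be the patient's true maximum and let attempt i read M − e_i, with e_i ≥ 0 the effort shortfall.

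- Mean of three: M − (e_1 + e_2 + e_3)/3.
- Largest of three: M − min(e_1, e_2, e_3).

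The minimum cannot exceed the average. The mean therefore carries at least as much shortfall as the largest value, with equality only when all three attempts fall short by the same amount. This needs no distributional assumption.

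**Step 2, between arms, attempts independent.** Assume exponential shortfalls with mean m, as a percentage of M. The mean of three falls short by m on average. The minimum of three independent exponentials has mean m/3, so the largest value falls short by m/3. With identical lungs in both arms:

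| Assumed mean shortfall by arm | Difference, mean of three | Difference, largest of three |
|---|---|---|
| 10% vs 10% | 0 | 0 |
| 12% vs 8% | 12 − 8 = 4.0 points | 4.0 − 2.7 = 1.3 points |
| 15% vs 5% | 15 − 5 = 10.0 points | 5.0 − 1.7 = 3.3 points |

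**Step 3, another shape.** Assume half-normal shortfalls with scale s in litres. The expected shortfall is about 0.80s for the mean of three and about 0.33s for the largest (1,000,000 simulated sessions).

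| Assumed s by arm | Difference, mean of three | Difference, largest of three |
|---|---|---|
| 0.10 vs 0.10 L | 0 | 0 |
| 0.10 vs 0.20 L | 0.080 L | 0.033 L |
| 0.15 vs 0.30 L | 0.120 L | 0.050 L |

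**Step 4, shortfall shared across attempts.** Pain is likely to persist through a session, so independence is doubtful. Let a fraction w of the mean shortfall m be common to all three attempts and the rest be independent exponential. The largest value then falls short by wm + (1 − w)m/3 = m(1 + 2w)/3. For 12% versus 8%, the mean of three gives 4.0 points throughout. The largest gives:

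- w = 0: 4.0 × 1/3 = 1.3 points
- w = 0.5: 4.0 × 2/3 = 2.7 points (8.0 vs 5.3)
- w = 1: 4.0 × 3/3 = 4.0 points

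**Step 5, limits.** Step 1 concerns each patient's value. The between-arm results in Steps 2 to 4 also assume that the arms differ in the amount of shortfall and not in its pattern across attempts. Separately, the largest value picks up upward random noise: the expected maximum of three independent standard normal errors is 0.85 SD. That cancels between arms when the noise is the same in both.

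**The case against.** The strongest reply has four parts.

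**Detail left out of an article.** A reader might infer that all four parameters are read from the forced breath, so that tidal volume and inspiratory capacity are invalid. The article does not say this. It does not exclude a quiet-breathing recording beforehand, and it refers to a standardized protocol that is not shown. This part stands: for those two parameters the text needs clarifying, and no measurement error is shown. It does not protect the averaging rule, which the article states outright and without exception.

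**The manoeuvre is right for FVC and FEV1.** This stands too. Forced exhalation is how these are measured; the point concerns only how the repeats are combined.

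**Pain-limited effort may be part of the effect.** A reader might call any effort-driven difference spurious, or say that one benefit is counted twice. The documents support neither. Pain relief is a plausible route by which fixation improves breathing, and the Statistical analyses section specifies no composite of pain and lung function. What remains is interpretation: whether a difference shows greater lung capacity or fuller effort.

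**The sizes are assumed.** This stands. No document gives effort shortfalls, their shape, their sharing across attempts, or any difference by arm. If the whole shortfall is shared, the largest value gains nothing, and otherwise it reduces the problem without removing it. But in every session it carries no more shortfall than the mean, so the direction does not depend on these assumptions.

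**Conclusion.** The averaging rule for FVC and FEV1 is a weak choice that should be changed. For a measure whose error is mainly downward, the mean of three carries at least as much effort shortfall as the largest value. A between-arm bias needs effort to differ by arm; unblinded patients and possibly unequal pain make that plausible but not established. Its size cannot be derived from the documents, and it is zero with equal effort. Under the assumed 12% versus 8%, it is 4.0 points with the mean and between 1.3 and 4.0 with the largest value.

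The article's silence on a quiet-breathing step for tidal volume and inspiratory capacity is a matter of clarity and does not make those two measures uninterpretable. The consequence is confined to one secondary outcome; the pneumonia endpoint and the sample size are unaffected.

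**What to change.** For FVC and FEV1, replace the mean of three with the largest value from the three acceptable efforts as the analysed value. Store every effort, so that the mean can be reported as a sensitivity analysis. Interpret both beside the pain score on maximal inspiration, which needs no new data collection.

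Reword the entry so that the forced-exhalation instruction applies to FVC and FEV1. State that tidal volume comes from a quiet-breathing recording, and inspiratory capacity from a maximal inspiration starting at resting end-expiration. If the full procedure already does this, only the text changes.

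The cost is a wording change and storage of the individual readings. If no quiet-breathing recording is made at present, it adds one to two minutes per session on the same device (an estimate, not a figure from the documents). The small downside is less comparability with studies that average, which reporting the mean as well largely offsets.

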## Methods/design

### Objective

The primary aim of this trial is to investigate the effect of ORIF versus nonoperative treatment on the occurrence of pneumonia within 30 days after trauma in adult patients who sustained multiple simple fractured ribs. The secondary aims are to investigate the effect of treatment on the need for and duration of mechanical ventilation, level of thoracic pain and analgesics use, (recovery of) pulmonary function, hospital and ICU length of stay, thoracic injury-related and surgery-related complications and mortality, secondary interventions, quality of life, and total costs (in-hospital and socio-economic) of treatment, health care consumption, and work absence. At the end, a cost-effectiveness analysis will be done.

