### Outcome measures

#### Primary outcome measure

The primary outcome measure is pneumonia within 30 days after trauma. In order to define pneumonia, the flowchart of the Centers of Disease Control and Prevention, based on imaging and clinical and laboratory criteria, will be followed (Fig. 1) [42]. Temperature (*T*) will be measured daily during admission. If *T* > 38.0 °C intra-auricular (or *T* > 39 °C rectal), bladder, central, or a sputum culture will be done. Also, the wound will be checked (if applicable) and a radiograph of the thorax will be made. If patients are suffering from fever at home, they will be advised to visit the outpatient clinic or emergency department. The temperature will be measured on arrival at the outpatient clinic or emergency department, and the same additional examinations will be performed. A monitor will independently review the patient’s medical files in order to ensure that the pneumonia was actually present.

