### Sample size calculation

Calculation of the required sample size for the primary analysis is based on data from a Cochrane review and a large retrospective analysis [7, 32]. These studies suggest a pneumonia rate of 35% in nonoperatively treated patients and 15% in operatively treated patients with multiple rib fractures. This difference is considered clinically relevant. A two-sided test with an α level of 0.05 and a β level of 0.2 requires 72 patients in each group. In order to account for 25% loss of patients to follow-up and mortality, a sample size of 90 patients per group is needed. In total, 180 patients will be included and randomized.

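### The mortality rate counts only deaths attributed to the thoracic injury, so deaths from the operation or anaesthesia are, on plain wording, left out of the comparison between arms

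*Protocol article*

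**What the plan says.** The rule stands in the protocol article, Secondary outcome measures, in the item on thoracic injury-related complications and mortality. It has two parts: "If mortality is caused by the thoracic injury or complication of thoracic injury, it will be counted in rates of mortality", and then "Death caused by other reasons will be noted but excluded in this calculation".

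The next item, on surgery-related complications, opens with "The ORIF group can also develop hardware-related complications or failure". It goes on to define superficial and deep wound infection and several forms of hardware failure. Death is not among them, and no other section defines all-cause mortality as an outcome.

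The Objective lists the secondary aim as "thoracic injury-related and surgery-related complications and mortality, secondary interventions", and the Methods part of the Abstract uses the same list.

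On blinding, Recruitment and randomization says that "patients and surgeons cannot be blinded for the intervention". Primary outcome measure provides for a monitor to review medical files independently, but the stated purpose is "in order to ensure that the pneumonia was actually present". The article does not say who decides the cause of a death, or whether that person knows the allocation.

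**The concern.** The trial tests an operation, and the gravest harm an operation can cause is death from the procedure or its anaesthesia. Such a death is caused neither by the rib injury nor, on an ordinary reading, by a complication of that injury. Under the stated rule it would be recorded but kept out of the rate on which the arms are compared. Only one arm is allocated to surgery, so this type of exclusion falls almost wholly on that arm.

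A cause-specific rate also needs someone to assign a cause to each death. Nothing described in the article protects that judgement from knowledge of the treatment. At stake is whether the reported mortality comparison can be trusted as a safety result. If the rate looks lower after ORIF, a reader could not tell fewer deaths from different labelling of deaths.

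**Working it through.** The article states no mortality rate, effect size or power for mortality, so there is no figure of its own to reproduce. The check has two parts.

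**1. The texts side by side**

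| Type of death | Thoracic item | Surgery-related item | Aim in Abstract and Objective |
|---|---|---|---|
| From the injury or its complication | Counted | Not listed | Named |
| From the operation or anaesthesia | Excluded on plain wording | Not listed | Can be read as named |
| From any other cause | Excluded | Not listed | Not named |

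The second row is the problem. The stated aim can be read as covering surgery-related death, but the outcome definitions place mortality under the thoracic item alone, and its causal condition leaves that death out.

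**2. What exclusion does to the rates**

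Inputs:
- 90 patients per arm (Sample size calculation; 180 randomized 1:1).
- All randomized patients are assumed to stay in the denominator.
- *d* is the number of deaths from any cause in each arm, assumed equal, so that the true difference is zero.
- *x* is the number of deaths classed as due to other reasons, in the ORIF arm (*x*_O) and in the nonoperative arm (*x*_N).

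Reported rate in an arm = (*d* − *x*)/90.

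Reported difference, ORIF minus nonoperative = −(*x*_O − *x*_N)/90.

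One excluded death changes an arm's rate by 1/90 = 1.1 percentage points.

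Illustration with *x*_O = 2 and *x*_N = 0. The death counts are assumptions, because the article supplies none:

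| Deaths per arm, any cause | True rate, both arms | Reported ORIF | Reported nonoperative | Apparent difference |
|---|---|---|---|---|
| 3 | 3.3% | 1/90 = 1.1% | 3/90 = 3.3% | −2.2 points |
| 5 | 5.6% | 3/90 = 3.3% | 5/90 = 5.6% | −2.2 points |
| 9 | 10.0% | 7/90 = 7.8% | 9/90 = 10.0% | −2.2 points |

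The apparent benefit is 2/90 = 2.2 points in every row. It depends only on the imbalance in excluded deaths. If the same number is excluded in each arm, the formula gives zero.

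**The case against.** Much can be said for the plan. Mortality is part of one secondary outcome and is unpowered, and the rule does not touch the primary pneumonia comparison. Other deaths are recorded, and reporting is to follow CONSORT, so the information should not be lost. The rule applies to both arms, and unrelated deaths over 12 months should be roughly balanced by randomization. The text never mentions operative deaths, and an assessor might class a perioperative death as a complication of the injury.

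These points limit the weight of the concern but do not remove it. Recording a death does not put it into the rate that is compared. And if inclusion depends on whether an assessor ties a perioperative death to the injury, the result rests on exactly the judgement that the article leaves unprotected.

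Some stronger readings are tempting, but the document does not support them:

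- *That the outcome is biased towards surgery by definition.* The direction and size depend on how many operative deaths occur and how they are attributed. The Abstract and Objective can also be read as including surgery-related mortality.
- *That the rule breaks intention to treat.* The death is left out of a calculation; the text does not say that the patient leaves the denominator.
- *That unblinded staff attribute cause of death.* The article does not say who does so. The weakness is that no safeguard is described.
- *That patients who die are treated as missing and imputed.* The phrase "In order to account for 25% loss of patients to follow-up and mortality" only enlarges the sample size. It sets no analysis rule, and the section on statistical analyses never says that deaths count as missing values.
- *That early deaths will pass as short stays.* Length of stay is defined by "This will be calculated as the time between admission and discharge from the hospital", without a rule for death. Such a rule is commonly left to the full protocol or analysis plan, neither of which is shown, so its absence is no finding.

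**Conclusion.** The concern holds for the mortality outcome only. As defined, the rate leaves out deaths from the operation or anaesthesia on plain wording, does not match the aim as worded in the Abstract and Objective, and is open to attribution that differs between arms in an unblinded trial. Where that happens, the likely beneficiary is ORIF, because operative deaths arise almost only there.

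The size is about 1.1 percentage points per reclassified death, given 90 patients per arm in the denominator. The net effect cannot be estimated. The Background cites mortality of up to 34% under nonoperative treatment of rib fractures, but that is the upper end of the cited series, while this trial excludes flail chest, patients with severe neurotrauma and those who are unstable or unfit for surgery. The figure is therefore no guide to the number of deaths here.

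The primary result is not directly affected. This is a near-free improvement to a safety outcome, and no sample size changes because mortality is not powered.

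**What to change.** - Make death from any cause, by randomized arm, the mortality outcome, reported at 30 days and at 12 months. Both are time points that the trial already uses.
- Report thoracic-related, surgery-related and other deaths as a descriptive breakdown of that total. Have the cause assigned, as far as possible, by someone who does not know the allocation.
- Reconcile the wording of the Abstract and Objective with the items under Secondary outcome measures, so that it is clear where surgery-related death belongs.

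The cost is a change of wording. Other deaths are already recorded, so no new data are needed. The change should be made before anyone analyses outcomes by arm, because a later choice of which deaths count would be hard to defend.

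### The surgery-related complications outcome covers only wound infection and hardware failure, so other operative harms are recorded but classified elsewhere

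*Protocol article*

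**What the plan says.** The Objective section of the protocol article lists surgery-related complications among the secondary aims and does not restrict them to hardware or the wound. The content of the outcome is given under Secondary outcome measures, where three neighbouring items matter.

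- **Thoracic injury-related complications.** This item names empyema, retained hydrothorax and nonunion and ends with an open category: "other (all other complications as judged by the treating physician". It also carries the grading rule: "Complications will be categorized for level of severity and treatment necessity according to the Clavien-Dindo classification".
- **Surgery-related complications.** The item opens with "The ORIF group can also develop hardware-related complications or failure" and explains both terms. The first is given as "Hardware-related complication is superficial and deep wound infection". For the second: "Hardware failure is defined as loosening of the plate, secondary dislocation of fixation material, malposition of hardware, and broken plates or splints". Neither explanation is marked as a list of examples, there is no open category, and grading is not mentioned.
- **Secondary interventions within 12 months.** Among the surgical examples are "evacuation of hematoma, evacuation of empyema, removal of failed hardware, symptomatic hardware removal, and treatment of infection". Among the indications for percutaneous intervention are "persistent bleeding intercostal artery, intraparenchymal bleeding, drainage of infection, and drainage of pleural fluid".

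Table 1 schedules the recording of complications before, during and after surgery and at every outpatient visit to 12 months. Study procedures adds that complications and secondary interventions are asked about at each follow-up visit and checked against the medical records.

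**The concern.** In a trial of operating against not operating, the outcome labelled surgery-related complications is the natural place to look for the price of the operation. A reader of the final report would take its rate as the frequency of operative harm in the ORIF arm. If the item admits only two kinds of event, the rate means something narrower than its label.

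The omission runs in one direction. A list that is too short can leave operative harms out of the rate, but it cannot add any. Where the omitted events go depends on attribution. Recruitment and randomization states that surgeons and patients are not blinded, so the physician who decides whether an event belongs to the injury category knows whether the patient was operated on.

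**Working it through.** No arithmetic applies. The article gives no expected rate for surgery-related complications, haematoma or symptomatic hardware, and there is no figure of the plan's own to reproduce. The check sets the items side by side.

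**Step 1: is the surgery-related item open or closed?** As printed it is closed. It has two components, each given a definition, with neither an example marker nor a residual category. The injury-related item just before it has a residual category, and the secondary-interventions item just after it marks its lists as examples. The section therefore uses open wording on both sides of this item but not in it.

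**Step 2: does the protocol foresee an operative harm outside those components?** Yes, at least one. The secondary-interventions item lists removal of failed hardware and, as a separate entry, removal of symptomatic hardware. The second entry must therefore include hardware that causes symptoms without having failed. Such hardware is not loose, dislocated, malpositioned or broken, and it need not be infected. It can exist only in a patient who has had fixation.

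**Step 3: do the bleeding entries show the same thing?** Only weakly. Haematoma, a bleeding intercostal artery and intraparenchymal bleeding can follow the operation, but they can also follow the blunt trauma. The interventions for them are listed without restriction to one arm. Some collections might also meet the injury-related definition of retained hydrothorax, which begins "a heterogeneous fluid collection with Hounsfield unit readings of" and goes on to give a range of 35–70. Bleeding supports the point only where it results from the operation.

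**Step 4: where does an unlisted operative harm go?**

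| Event after fixation | Surgery-related item | Injury-related item | Secondary interventions |
|---|---|---|---|
| Wound infection; hardware failure | Named | Not needed | If treated |
| Symptomatic intact hardware | Not named | Only through the open category | If removed |
| Postoperative bleeding or haematoma | Not named | Open category, or possibly hydrothorax | If evacuated or embolised, for example |
| Iatrogenic injury; anaesthetic event | Not named | Only through the open category | Only if it leads to an intervention for a rib fracture-related problem |

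Every row has a place somewhere, but only the first row reaches the surgery-related rate. Secondary interventions are a partial backstop, because a harm that is tolerated or managed without an intervention does not appear there.

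**Step 5: is severity graded?** The Clavien-Dindo sentence stands in the injury-related item. It may be meant for both items, but the text does not say so.

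**The case against.** The strongest reply is that the two complication items are meant to be read together. The surgery-related item says that the ORIF group can *also* have hardware problems, which makes it an addition to the preceding list, and that list ends with all other complications. On this reading no operative event is without a place. Symptomatic hardware removal and haematoma evacuation are also counted in a named outcome of their own. The source is a journal article, and itemised complication forms and attribution rules usually sit in the full protocol or the case report form.

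Much of this stands. A reader might infer that operative harms go unrecorded. The documents do not support that: Table 1 and Study procedures provide for their collection throughout follow-up, and the open category is broad. A reader might also count the listed interventions that have no matching named complication and treat the share as a measure of the gap. That fails because the intervention lists are examples, so there is no meaningful denominator, and because the bleeding entries are not specific to surgery. Nor can a percentage of missed harms be assumed and then reported as the understatement, since that only returns the assumption.

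Two things do not fall away. If the open category takes in operative events, they are reported under a thoracic injury label, which is the misclassification at issue. And the point does not rest on detail that an article leaves out: the article states what the surgery-related item consists of, and that statement is too narrow for its label and for the interventions listed next to it.

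**Conclusion.** The point holds as one of classification. Read as printed, the surgery-related outcome counts wound infection and hardware failure and omits other operative harms, at least one of which the same section expects to treat. Those harms remain in the trial data, but under an injury-labelled category that depends on unblinded judgement, or as secondary interventions.

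The direction is clear: the surgery-related rate can only be too low as a measure of operative harm. The size cannot be estimated from the documents. The conclusion assumes that the full protocol or case report form does not already add an open surgery-related category; if it does, only the article's wording is at fault.

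A reader might infer that the between-arm comparison of harm is biased as a whole. The documents do not support that, because the injury-related complications and secondary interventions apply to both arms and the underlying events are collected. The matter is minor and concerns one secondary outcome. The primary outcome, its test and the sample size are unaffected.

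**What to change.** Make two changes.

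1. **Widen the item.** Add symptomatic intact hardware, and an open category for other surgery-related complications that names bleeding, iatrogenic injury and anaesthetic events as examples. State that the whole item is graded by Clavien-Dindo.
2. **Add a table that needs no attribution.** Report all complications to 12 months by allocated arm regardless of attributed cause: the proportion of patients with any complication, and with one of grade III or higher.

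The first change makes the rate match its label but still relies on an unblinded decision about cause. The second removes that dependence, so the two belong together.

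The cost is small: one outcome reworded and one more table, from data already scheduled in Table 1, with no additional visits or patients. The downside is a longer report and a possibly less favourable complication rate for ORIF.
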